#### Measures for studying processes and implementation of the interventions

The study coordination bureau of the GQNS receives a study report by 3M on a quarterly base that informs about the quality indicators of each participating hospital as well as about hospitals that failed to provide their claims data. Hospitals that do not provide their claims data despite several reminders are excluded from the quality collaborative. To assess fidelity and dose of the local implementation of interventions in the participating hospitals, the coordination bureau of the GQNS regularly surveys local QI team leaders by standardized online questionnaires. These questionnaires contain items regarding departments participating in the QI teams, extend of interdisciplinary analyses of quality indicators, extend of interdisciplinary case analyses, extend of education of staff, and implementation of further interventions like existence and scope of rapid response teams. The questionnaire also contains items regarding barriers to change like lacking resources or support by management, as well as items that evaluate the quality of tools and support provided by the coordination bureau. The questionnaire was developed based on results of qualitative interviews conducted during the MEDUSA trial [30]. Peer-review visits are documented and evaluated using paper-pencil surveys using standardized questionnaires both by the external peers and the involved local clinicians. These questionnaires were adapted from existing tools used in other German quality initiatives [67, 73].

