### Analyses

#### Analysis of the primary outcome

The final analysis of the intervention effect will be conducted using German national DRG data. The change in hospital mortality between the baseline period (January 2014 to December 2015) and the intervention period (April 2016 to March 2018) will be compared between the 48 hospitals initially enrolled in the GQNS and control hospitals. These are all non-participating German hospitals, whose DRG data are also available from the Federal Bureau of Statistics. Hospitals entering the GQNS after March 2016 will be excluded from this comparison. This comparison will be conducted in 2020 when the national DRG data for 2018 will be available from the Federal Bureau of Statistics. The primary analysis will evaluate the difference-in-differences in a hierarchical generalized linear model controlling for clustering of cases in hospitals by testing the statistical interaction between period (baseline vs. intervention) and group (48 hospitals enrolled in GQNS vs. control hospitals). Patient-related risk-factors will be considered as covariates. As a secondary analysis, the trajectories of change across time before and after intervention will be compared between intervention and control hospitals by a piecewise hierarchical model [74].

A preliminary evaluation of the study effect will be performed after completion of the intervention period in March 2018 but only relying on the data of the 48 intervention hospitals (before-after-comparison). A secondary preliminary analysis will be done by a piecewise hierarchical model to investigate the change in the trajectory of hospital mortality over time between periods.

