#### Sensitivity analyses and planned subgroup analyses

Differences across time between hospitals of the GQNS and control hospitals might result from changes in coding in the intervention hospitals, e.g., improved ICD-coding of sepsis or comorbidities. Therefore, incidences of sepsis without organ dysfunction, sepsis with organ dysfunction and septic shock as well as incidences of mortality risk-factors will be compared across time between intervention and control hospitals. Analyses of the primary outcome will be repeated within these three subgroups of sepsis cases.

Additionally, hospitals will be categorized based on the degree of their QI efforts during the intervention period but without inspection of their primary outcome. The categorization will be based on the results of the regularly conducted surveys of local QI team leaders. The analyses of the primary end-point will be repeated within the subgroups of hospitals with high QI effort and hospitals with low QI effort.

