#### Sample size considerations

Concerning the baseline period (January 2014 to December 2015), 45,419 cases with sepsis were included among the initially enrolled 48 hospitals, of which 27,331 (60%) were diagnosed with sepsis with organ dysfunction (including septic shock), resulting in approximately 1000 cases per hospital across both the baseline and intervention period. Comparing the intervention hospitals with all other German hospitals across a baseline and intervention period resembles a controlled before-after trial on the cluster level. Therefore, our sample size calculation used a design factor developed for cluster-randomized before-after trials [75]. We observed a baseline mortality of 44% and an interclass correlation (ICC) of 0.02 among the included 48 hospitals. Based on the results of the Surviving Sepsis Campaign [15], a reduction in mortality to 40% was expected for the 2-year intervention period. A Fisher’s exact test comparing intervention and control conducted at α-level 0.05 with a power of 0.9 would require a total sample size of 6476. Correcting this sample size by the obtained design factor of 3.75, a total of 26 hospitals (13 control and 13 intervention) each including 1000 cases would be necessary in a cluster randomized before-after trial. Given 48 intervention hospitals and more than 1000 control hospitals in the national German DRG data, our study should be adequately powered to detect the expected intervention effect.

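### The plan repeats the primary analysis separately in high-effort and low-effort hospitals but names no test of the difference between them and no comparator for either subgroup

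*Protocol article*

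**What the plan says.** The primary analysis (protocol article, Analysis of the primary outcome) is a difference-in-differences in a hierarchical model, carried out by "testing the statistical interaction between period (baseline vs. intervention) and group (48 hospitals enrolled in GQNS vs. control hospitals". On the controls, the same section says: "These are all non-participating German hospitals, whose DRG data are also available from the Federal Bureau of Statistics".

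The section on sensitivity and planned subgroup analyses adds an analysis by quality-improvement (QI) effort. Hospitals will be "categorized based on the degree of their QI efforts during the intervention period but without inspection of their primary outcome". The source of the rating is given next: "The categorization will be based on the results of the regularly conducted surveys of local QI team leaders". The analysis itself is then stated in one sentence: "The analyses of the primary end-point will be repeated within the subgroups of hospitals with high QI effort and hospitals with low QI effort".

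The section on measuring processes and implementation shows who is rated. To assess how participating hospitals implement the interventions, "the coordination bureau of the GQNS regularly surveys local QI team leaders by standardized online questionnaires". Control hospitals therefore have no effort rating.

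**The concern.** Splitting hospitals by effort has little purpose other than to learn whether the effect differs by effort. The stated method gives two separate results, each answering whether that subgroup changed differently from its comparator. Neither answers whether the subgroups differ from each other, and the pair has no controlled error rate for that question. A report of an effect in high-effort hospitals only would readily be taken as a dose-response, although identical true effects can produce the same pattern.

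The comparator is also left open. The same section repeats the primary analysis in subgroups of sepsis cases, which works because both network and control hospitals have such cases. For effort, a subgroup taken literally contains no controls. A reader cannot tell whether each half is set against all controls or only before against after. The protocol's own Discussion says that uncontrolled before-after comparisons cannot separate an intervention effect from secular trend.

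**Working it through.** **1. The protocol's own sample size.** Its test is "conducted at α-level 0.05 with a power of 0.9 would require a total sample size of 6476", for mortality of 44% against 40%. The two-sided two-proportion formula is

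n per group = [1.96·√(2·0.42·0.58) + 1.2816·√(0.44·0.56 + 0.40·0.60)]² / 0.04² = 3198,

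so the total is 6396, or 6496 with continuity correction. The stated 6476 for Fisher's exact test lies between the two.

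**2. The design factor.** Take 500 cases per period and ICC 0.02. The cluster inflation is 1 + 499·0.02 = 10.98, and r = 500·0.02/10.98 = 0.911. Then 2·(1 − r²)·10.98 = 3.745, matching 3.75. Next, 6476·3.75 = 24,285 cases, or 12.14 hospitals of 1000 per arm, rounded up to 13 + 13 = 26. The sample-size section is not at fault. It gives no figure for the effort subgroups.

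**3. Inputs for the subgroup check.**
- From the protocol: "We observed a baseline mortality of 44% and an interclass correlation (ICC) of 0.02 among the included 48 hospitals"; expected mortality 40%; 27,331 baseline cases in 48 hospitals, so 27,331/48 = 569 per hospital per period; more than 1000 control hospitals.
- Assumed, because the protocol does not give them: a 24/24 effort split (12/36 as an alternative), exactly 1000 controls, equal-sized hospitals, between-period cluster autocorrelation ρ from 1.0 to 0.8, and a normal approximation on hospital-level changes.

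**4. Standard errors at 24/24.** With v = 0.42·0.58 = 0.2436, the variance of one hospital's change is V = 2·[0.98·v/569.4 + 0.02·v·(1 − ρ)].
- ρ = 1.0: V = 0.000839. Subgroup against controls: √(V·(1/24 + 1/1000)) = 0.0060. High against low: √(V·2/24) = 0.0084.
- ρ = 0.8: V = 0.002787. The same two standard errors are 0.0109 and 0.0152.
- The ratio is 1.40 in both cases.

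**5. Chance that exactly one of the two tests is significant when the true effects are identical.** With power q for each test, q = Φ(effect/SE − 1.96), and the chance is close to 2q(1 − q). For 2 points, q is 0.917 (ρ = 1.0) or 0.450 (ρ = 0.8), giving 0.15 and 0.495. For 4 points at ρ = 0.8, q = 0.956 and 2·0.956·0.044 = 0.084. Simulation with 400,000 draws and shared controls gives:

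| True effect in both subgroups | 24/24 split | 12/36 split |
|---|---|---|
| 4 points (planned) | under 0.1% to 8.5% | 0.3% to 26% |
| 2 points | 15% to 49% | 34% to 57% |
| 1.5 points | 40% to 47% | 42% to 55% |

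Each range is over ρ = 1.0, 0.9 and 0.8. Sharing the controls hardly matters: the correlation between the two tests is (1/1000)/(1/24 + 1/1000) = 0.023. The gap between 8.4% and 8.5% is simulation error.

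**6. The direct contrast.** A test of high against low by period holds the false-difference rate at 5% under the same model. The controls cancel, so no control needs a rating. At 24/24 its power is 99.8% to 75% for a 4-point difference in effect, and 67% to 26% for a 2-point difference.

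**The case against.** The strongest case on the other side has five parts.

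- **Unrated controls.** A reader might infer that the analysis cannot show whether effort matters because controls have no rating. The document does not support that. The primary analysis defines one control group that can serve both subgroups, and this is the natural meaning of repeating it. Two estimates with standard errors would also let a reader work out the difference. What stands is that the comparator should be named and the difference reported.
- **Size.** A reader might apply 2q(1 − q) with 80%, 70% or 50% power per half and quote 32%, 42% or 50% as this trial's risk. Those powers are not derived from the protocol. At the planned effect and an even split, disagreement is far rarer. It becomes common only if the true effect is well below plan. That is possible: the Discussion concedes that two years may be too short for a substantial effect.
- **No claim of effect modification.** The protocol states no dose-response hypothesis, and it says elsewhere that the analyses cannot tell which intervention elements caused a change. This is a non-primary analysis. That stands, and it limits the weight of the point.
- **Detail left to the analysis plan.** A contrast may exist in a plan that is not shown. But the article does not leave the method open: it commits to separate repeats, and the point concerns that method.
- **Outcome-dependent ratings.** Keeping the primary outcome from whoever does the categorizing does not make effort independent of outcome. Hospitals receive quarterly mortality reports, and peer review is suggested to those with high mortality ratios. Against this, the questionnaire asks largely about implementation facts, and bias in the answers is conjecture. This supports an observational label and nothing stronger.

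**Conclusion.** The point holds in a limited form. The stated method gives two subgroup results and no test of their difference, and it leaves the comparator unnamed. One subgroup significant and the other not would not show that effort matters.

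The size depends on the true effect. With an even split it is negligible to modest at the planned 4 points and substantial at about 2 points. An uneven 12/36 split raises it, to as much as 26% even at 4 points. All these figures rest on the assumed split, number of controls, equal hospital sizes and autocorrelation.

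The primary analysis and the sample-size calculation are unaffected. Even a proper contrast would be associational, because effort is self-reported, measured after baseline, not randomized, and may respond to the mortality reports.

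**What to change.** 1. Name all control hospitals of the primary analysis as comparator for both effort subgroups.
2. Replace the two separate runs with one hierarchical model with group at three levels (control, low-effort, high-effort) by period and the same patient covariates. Report each subgroup's change against controls, and the high-minus-low contrast in change with its confidence interval.
3. Label the contrast exploratory and observational, and state why.
4. Keep the categorization over the whole intervention period, as planned. A categorization on the August 2016 survey alone may be added as a sensitivity analysis. It should not be the main rule: the first online lectures (March 2017) and first peer reviews (May 2017) came later, so it would miss them, and the first mortality reports had already gone out in March 2016.

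The cost is small: no new data, one model in place of two, and one added contrast. That contrast has a standard error about 1.4 times that of a subgroup-versus-control estimate at 24/24, so a wide interval should be reported as inconclusive, not as evidence that effort makes no difference.

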#### Sample size considerations

Concerning the baseline period (January 2014 to December 2015), 45,419 cases with sepsis were included among the initially enrolled 48 hospitals, of which 27,331 (60%) were diagnosed with sepsis with organ dysfunction (including septic shock), resulting in approximately 1000 cases per hospital across both the baseline and intervention period. Comparing the intervention hospitals with all other German hospitals across a baseline and intervention period resembles a controlled before-after trial on the cluster level. Therefore, our sample size calculation used a design factor developed for cluster-randomized before-after trials [75]. We observed a baseline mortality of 44% and an interclass correlation (ICC) of 0.02 among the included 48 hospitals. Based on the results of the Surviving Sepsis Campaign [15], a reduction in mortality to 40% was expected for the 2-year intervention period. A Fisher’s exact test comparing intervention and control conducted at α-level 0.05 with a power of 0.9 would require a total sample size of 6476. Correcting this sample size by the obtained design factor of 3.75, a total of 26 hospitals (13 control and 13 intervention) each including 1000 cases would be necessary in a cluster randomized before-after trial. Given 48 intervention hospitals and more than 1000 control hospitals in the national German DRG data, our study should be adequately powered to detect the expected intervention effect.

### Ethical considerations

The study underwent review by the internal review board of the Jena University Hospital (IRB protocol 4536-08/15) and the data protection supervisor of the Free State of Thuringia, Germany. Since individual case data are only obtained in the form of pseudonymized claims data, the need for informed consent by patients was waived. Quality reports present only aggregated data by hospital. Hospital names are pseudonymized, and each hospital knows only its own pseudonym. Only 3M and the study coordination bureau can de-pseudonymize all hospitals. Individual case data are only reported to the hospital where the cases were treated. For all kinds of surveys of QI team members, hospital staff, or peer-reviewers, participants will be informed about aims of the surveys and methods for protection of data privacy. Informed consent will be implied by participation in the survey, survey data will be stored in pseudonymized or anonymized form only, and all public reports of survey data will contain only aggregated data allowing no identification of individual participants.

### Project status

The GQNS was officially started with a kick-off meeting in February 2016. The first quality reports were distributed in March 2016 to the initially enrolled 48 hospitals. Till October 2017, quality reports have been distributed five times. Based on the public awareness of the GQNS, additional hospitals entered the network after the active recruitment. In September 2017, the number of participating hospitals reached 75, clearly surpassing the initially planned number. Participating hospitals are located all over Germany and include hospitals of all levels of care, among them 18 university hospitals (of 39 in Germany). In August 2016 and August 2017, two surveys of local QI team leaders were performed to assess the current progress and barriers to change in the participating hospitals and results were reported to senior hospital managements. Between March 2017 and September 2017, the first four online lectures and between May 2017 and September 2017 the first three external peer-reviews took place.

## Discussion

The goal of this project is to establish structures for quality improvement of care for patients with sepsis and thereby to decrease sepsis-related in-hospital mortality. The GQNS is the first quality collaborative using claims data and a complex risk-adjustment to measure and improve quality of care for patients with sepsis. Because of this pragmatic approach 75 hospitals signed contracts for participation.

Previous QI initiatives to improve sepsis care relied on gathering prospective clinical data in an uncontrolled before-and-after design [15, 17–21]. Based on these studies, it is impossible to distinguish the intervention effects from general secular trends [71]. The first cluster-randomized trial which set out to test for effects of elements of a QI collaborative on sepsis-related mortality (MEDUSA trial) failed partly because of incomplete and delayed inclusion of cases with sepsis. Our study design overcomes both of these shortcomings. Using claims data makes all patients with coded sepsis available for analysis. Based on a German national claims database, it is possible to evaluate the effect of the QI initiative in a difference-in-differences design comparing intervention hospitals to all other German hospitals.

The approach of our study of course has some limitations. First, under- or over-coding of sepsis might occur in claims data [76]. However, for every hospital, the degree of under-documentation has decreased considerably, as since 2007 appropriate coding of sepsis cases has become a financial interest for the hospitals. On the other hand, over-coding of sepsis cases for financial reasons is systematically controlled for by the Medical Review Board of the Statutory Health Insurance Funds. A second limitation is the time-lag of 1.5 years until German national claims data are available for analysis delaying the final analysis of the intervention effect. A preliminary evaluation of the effect can only rely on data of the intervention hospitals. Finally, quality improvement in sepsis care has been described to be a marathon and not a short sprint [77]. The 2-year intervention period of the start-up phase of the GQNS might be too short for attaining substantial effects on hospital mortality in a large sample of hospitals. The aim of this start-up period is to build a long-lasting quality initiative and to establish structures for sustained quality improvement. A reevaluation of the effects of participating in the GQNS after a longer period of time—comparable to the duration of other successful large-scale QI initiatives [15]—might be necessary.

If this study finds that the approach of using claims data in combination with a complex risk-adjustment is useful for measuring and improving quality of sepsis care, the approach may also be applied to other diseases.

## Appendix

### Definition of cases with sepsis by German ICD-10 codes

Sepsis without organ dysfunction: A40.0, A40.1, A40.2, A40.3, A40.8, A40.9, A41.0, A41.1, A41.2, A41.3, A41.4, A415.1, A41.52, A41.58, A41.8, A41.9, R65.0.

Sepsis with organ dysfunction but without septic shock: R65.1.

Septic shock: R57.2.

## Abbreviations

3M: 3M Health Information Systems
CSCC: Center for Sepsis Control and Care
DRG: Diagnostic related groups
GQNS: German Quality Network Sepsis
MEDUSA trial: Medical EDUcation for sepsis Source control and Antibiotics, ClinicalTrials.gov identifier NCT01187134
QI: Quality improvement
RSMR: Risk standardized mortality rate
SMR: Standardized mortality ratio
